# Randomization and blinding

## In this study, allocations with a ratio of 1:1 will be performed through an online randomization program (<https://www.randomizer.org/>) by an independent researcher, who will be excluded from any other activity throughout the intervention. The unit of randomization is the patient-FC dyad. The randomization list will be stratified by the type of relationship between the patients and caregivers (e.g., spousal relationship vs. non-spousal relationship) with a block size of 4 or 6. The allocation sequence will be printed and sealed separately in opaque envelopes by the randomizer.

## The staff nurses in the study hospital will enroll dyads of patients and caregivers. After the baseline assessment is completed, the dyad’s registration data will be given to the research coordinator. The research coordinator will open the envelope and then enter the data into the database and assign dyads to interventions. The participants will be informed of their allocation status via smartphone when the research coordinator plans to schedule the first session.

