# Outcomes

The characteristics of the participants will be gathered at baseline before the intervention, including: (1) their sociodemographic data, such as their age, gender, educational attainment, employment, and relationship with each other; and (2) their clinical data, such as patients’ NHYA classification, length of time that they have had the disease, comorbidities and activities of daily living (ADL), and caregivers’ length of caregiving. The effectiveness of the interventions will be evaluated at the dyadic level and individual level for patients and their caregivers at baseline, immediately post-intervention, and at 3 months post-intervention.

All health outcome assessments will be tested using reliable and valid scales. The research assistants have been fully trained in outcome assessments to ensure quality and consistency; they will interview patients with CHF and their FCs to complete the online assessments (http://www.wenjuan.com/) via smartphone in a private office. Participants who discontinue the intervention will be encouraged to participate in the outcome assessments.

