# Data management

A detailed database will be established to record the assessments and progress of each participant. Each participant will assign a unique identifier to preserve their confidentiality. This database will be password-protected and only accessible to authorized members of the research team. The researcher coordinator will monitor the data collection process, quality, and safety periodically. Any adverse events will be identified, documented, and handled with the caution. In cases of discrepancies, the research team including experts in cardiologist, nurses, and academia, will discuss and reach a consensus. Consultation with clinical trials specialists in the study hospital will be sought if required.

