**Ethical considerations**

Ethical approval for this study was given by the institutional review board (IRB) of the Hong Kong Polytechnic University (reference: HSEARS20210225006; 23-Apr-2021) and the Taihe hospital (Version 3; reference: 2022KS013; 3-Jun-2022;). Oral consent and verbally recorded informed consent will be obtained from each patient and family caregiver before a baseline assessment and randomization are conducted. Participation in the study is completely voluntary for CHF patient-caregiver dyads, and they are free to withdraw from the study at any point without consequences. Participants' identities and data, including information collected and video/audio records, will be kept confidential and anonymous to safeguard their privacy. Only authorized personnel will be allowed access to the data for analysis purposes.

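### The coordinator opens the allocation envelope before entering the dyad in the database, and no stated step ties a dyad to an envelope before the arm is seen

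*Protocol*

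**What the plan says.** All of the allocation procedure stands in the Protocol, section Randomization and blinding.

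- An independent researcher generates a 1:1 list, stratified by spousal or non-spousal relationship, in blocks of 4 or 6. This is a person "who will be excluded from any other activity throughout the intervention".
- On concealment: "The allocation sequence will be printed and sealed separately in opaque envelopes by the randomizer".
- On enrolment: "The staff nurses in the study hospital will enroll dyads of patients and caregivers".
- On what comes next: "After the baseline assessment is completed, the dyad’s registration data will be given to the research coordinator".
- On opening: "The research coordinator will open the envelope and then enter the data into the database and assign dyads to interventions".
- The dyad learns its arm later, by smartphone, when the coordinator arranges the first session.

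Three other sections bear on the point. Ethical considerations says: "Oral consent and verbally recorded informed consent will be obtained from each patient and family caregiver before a baseline assessment and randomization are conducted". Outcomes says of the research assistants that "they will interview patients with CHF and their FCs to complete the online assessments". Data management gives the coordinator a further task: "The researcher coordinator will monitor the data collection process, quality, and safety periodically".

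**The concern.** With sealed envelopes, the safeguard against manipulation is that a named participant is tied to a given envelope before anyone sees what is inside. Here the stated order is to open, then enter, then assign, and one person does all three. That person also schedules the first session and monitors data collection. No second person is described who would see a mismatch between envelope and dyad.

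Two things are at stake. First, the Statistical analysis section compares the groups as randomized, which requires every opened envelope to be traceable to the dyad it was meant for. Second, dyads and interventionists are not blinded and the primary outcomes are self-reported quality of life, so sound allocation is one of the trial's main protections.

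A departure need not involve bad faith. Sessions take four to eight dyads (section Interventions), so whoever fills the groups could have a logistical reason to prefer one arm for a given dyad. That motive is an inference; the protocol does not suggest it.

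**Working it through.** No arithmetic decides this point. The check is to put the stated steps in order and ask, at each one, what record exists and who made it.

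1. **Before opening, consent.** Ethical considerations places consent before both baseline and randomization. It is verbally recorded.
2. **Before opening, enrolment.** Staff nurses do this, not the coordinator.
3. **Before opening, baseline.** Research assistants interview both members, and the answers go into an online form.
4. **Before opening, handover.** Registration data pass to the coordinator.
5. **Opening.** The coordinator learns the arm.
6. **After opening.** The coordinator enters the data in the database and assigns the dyad.

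Steps 1 to 4 show that the dyad exists and has been enrolled. None of them says which envelope belongs to it. The link between dyad and envelope is first recorded at step 6, after the arm is known.

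Next, does any other stated feature create that link earlier?

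- **Sealing and opacity** hide the contents before opening. They do not bind an envelope to a dyad.
- **Stratification** means that a dyad should draw from the envelopes of its own relationship stratum, so an exchange across strata should be visible. An exchange within a stratum would not be.
- **Sequential numbering, an identifier on the envelope, or a log completed before opening** would each create the link. None is stated.
- **Independent generation of the list** protects the sequence. The list could be reconciled with what was assigned only if the order of use were recorded, and no such record is described.

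Two departures are therefore possible:

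- **Swap within a stratum.** Envelopes opened for two dyads of the same stratum are exchanged before entry. Both dyads appear in the database with an arm, and nothing there shows the exchange.
- **Opened but unentered allocation.** An envelope is opened and its result not entered. The database shows nothing. If the dyad is dropped as well, its consent and baseline records remain elsewhere. If another envelope is used for it, they do not reveal the change.

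The planned size is not involved. For an effect size of 0.50, power 0.80 and a two-sided 0.05 level, the two-sample t-test needs 63.77, so 64 per arm and 2 × 64 = 128 in total. Then 128 / (1 − 0.20) = 160 dyads, as the Sample size calculation section states.

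**The case against.** The strongest reply is that the usual selection risk, an enroller who knows the next arm, is handled. The sequence comes from an independent person, the envelopes are opaque and separately sealed, other staff enrol, and consent and baseline come first. This stands. A reader might infer from the order of opening and entry that dyads are enrolled with the arm known, or that the arm is known before registration is irrevocable. The document supports neither. It never says when registration becomes final or that database entry is the act that makes it so, and registration data already exist when the envelope is opened.

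A second reply is that the data to be entered may be the allocation itself, which can only be entered after opening. That reading is possible. It is the less natural one, because the preceding sentence has just handed over the dyad's registration data. Even on that reading, no earlier step linking dyad to envelope is stated.

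A third reply is that numbering and logging often sit in an operating manual. That is fair, and silence on numbering alone would not be a fault. The point rests on an order that the protocol does state, in the weaker direction.

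A reader might also add that someone who opens every envelope can anticipate later allocations within a block. That is a separate matter. It does not depend on whether opening or entry comes first, and reordering would not change it.

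**Conclusion.** The point holds in a limited form. As written, the arm is seen before the dyad is entered, and nothing stated ties dyad to envelope beforehand. Enrolment is protected; the gap is confined to the one person who opens, enters and assigns. Its consequence is a loss of traceability within a stratum.

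The size of any bias cannot be derived from the document, and nothing shows that allocations would in fact be altered. The conclusion assumes that the data to be entered include the registration data, and that no operating procedure outside the protocol already supplies the missing link. It is a small, free improvement and does not threaten the trial's design.

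**What to change.** Reword the step in Randomization and blinding so that the coordinator:

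1. enters the dyad's identifier, relationship stratum and baseline date in the database;
2. writes the identifier on the next sequentially numbered envelope of that stratum;
3. only then opens the envelope and records the arm.

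State also that the independent researcher numbers the envelopes in sequence within each stratum when sealing them. If a manual already requires this, a sentence in the protocol saying so is enough.

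The cost is the rewording and the numbering. No extra staff are needed, and the design, sample size and analysis do not change.

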## The research assistants serving as outcome assessors in this study will be blinded to the group allocations; they will be unable to access the participants' intervention conditions during the program. During the follow-up assessments, the outcome assessors will remind the participants to remain blind to their group assignment throughout the study and ask them to conceal their status during the outcome assessments. If this blinding is breached for any reason, another research assistant who is unaware of the group condition of the dyads will take over the phonic assessment. Participating dyads and interventionists will not be blinded because of the nature of the psychoeducational intervention.

# Interventions

Participating dyads will be allocated to either the intervention group or the control group. All of them will receive four identical weekly sessions via the Tencent VooV meeting over four consecutive weeks in addition to the usual care provided by the department of cardiology. Each session will include four to eight dyads and last approximately two hours, and will be led by a registered nurse(s) with technical support from two research assistants throughout the sessions. Participants will receive relevant materials and handouts prior to the first session, and they will be instructed to retain these materials and handouts throughout the duration of the study and beyond. The online sessions will be scheduled on weekday evenings and weekend afternoons to accommodate typical family events and work schedules. During the period of the interventions, WeChat voice calls or text message reminders will be sent to the dyads before each session to improve participant retention and support engagement in the program.

# Intervention group: ACT-based intervention (ACT group)

Each session in the intervention group will consist of group ACT (1.5 hours) and brief CHF education (0.5 hours) conducted by two trained registered nurses as facilitators. The ACT intervention covers six interrelated core processes to produce psychological flexibility by using metaphor illustrations, experiential exercises, and guided mindfulness exercises, while the contents of the brief CHF education only include information on CHF self-care. Prior to the session, the participant will receive an additional packet supporting the practice of ACT exercises in the sessions, which will include black and white cards, whiteboard markers, two small packages of raisins, and one towel, in addition to one set of CHF self-care materials. The handouts for this group consist of information on CHF self-care, ACT skills, and homework assignments making changes to the ACT processes targeted in each session. Participants will be asked to maintain the confidentiality of the intervention content and avoid discussing it with participants in the control group to prevent contamination.

**ACT-based intervention development**

The first version of the ACT intervention protocol was informed by the ACT classic therapist manual (32, 45-51) and literature on the experiences of CHF patients and FCs (52-56), previous ACT trials with chronic illness patients and FCs (57-61), and an ACT intervention at the dyadic level (36, 62-64). The intervention protocol (Version 1) was initially evaluated in a 4-week uncontrolled clinical trial through an in-person format (𝑁 = 5). This led to some adaptations of the ACT intervention in relation to the dyads. Afterward, the intervention protocol was refined and adopted in an online videoconference format (Version 2). The intervention protocol (Version 2) was retested in a 4-week pilot RCT via smartphone without a follow-up assessment (𝑁=14); the findings indicated that further refinements were required of some experiential exercises, and they informed the revision of the intervention protocol (Version 3) before the commencement of its implementation in this RCT. All versions were finalized by the research team and informed by feedback from the participants and facilitators, the facilitators’ direct observations during the delivery of the intervention, and input from the ACT expert. Any disagreements were discussed with the chief supervisor and resolved by consensus.

The four-session group-based ACT intervention includes exploring participant’s control agendas, identifying their values, exploring their thoughts and feelings, and finding ways to take committed actions in line with the personal values that they hold. The first ACT sessions are aimed principally at exploring previous control-based strategies to attempt to cope with private experiences and the workability of control when pursuing meaningful lives. The following session starts with a review of the processes in which the participants were instructed in the previous session and the between-session assignments. From the second session, the facilitators will focus on increasing connection with life values and commitment to values-based actions. Individual values will be identified, while alternative behavior related to the participants’ values will be clarified. Patient-FC dyads will have the opportunity to share their values and alternative value-based actions to manage CHF situation with each other. Potential cognitive and emotional barriers in the context of home care to adopt alternative behavior and preserve value-driven long-term action will be explored and addressed via illustrations using metaphors and by practicing experiential exercises. Participants will be encouraged to be more accepting and compassionate, detach themselves from self-conceptualizing, take a flexible perspective, and develop flexible attention. Throughout the program, facilitators will facilitate dyadic sharing and reflect on their experience, which in turn will promote the establishment of supportive relationship bonds.

**Facilitator training and fidelity checks**

Two registered nurses will deliver the ACT intervention to the patient-FC dyads. The primary facilitator is also a doctoral student in nursing who has completed a total of 7 days of ACT workshops and a guided online 21-day ACT action camp led by ACT experts worldwide and in China. The co-facilitator is a registered nurse at the local hospital who holds a bachelor's degree in nursing and has received two days of introductory-level training in ACT led by ACT experts in China. Both of them have at least three years of experience working with cardiac inpatients and have co-facilitated the delivery of about eight sessions of a group-based ACT intervention for patient-FC dyads. The facilitators' prior training will be supplemented through role-play practices using the finalized version of the intervention protocol for this study before the commencement of this study.

To monitor the facilitators' competence and fidelity to the contents of the intervention protocol, each group session will be video-recorded with participant’s consent and reviewed independently by facilitators immediately after the session by using the ACT core competency self-rating form (65). Inter-rater agreement will be established before the implementation, while the intra-class correlation (2,1) for each session will be calculated. Feedback on fidelity will be discussed during an in-person meeting after each session. Besides peer coaching, regular bi-weekly supervision and timely supervision will be provided by an experienced ACT researcher to ensure adherence to the intervention protocol throughout the program. The doctoral degree student facilitator and her supervisor will together review the difficulties encountered during the sessions. If any area for improvement is identified, the primary facilitator will provide a remedy before the next session.

# Control group: CHF education (CE group)

CHF education only as an active control was chosen because knowledge of CHF is a foundational and essential component to empower patients with CHF and their FCs to manage CHF in the family context (66).

The sessions for the CHF education control will be delivered by one registered nurse who holds a bachelor's degree in nursing and has at least three years of experience working with cardiac inpatients. Each 2-hour session includes a review of the previous session, didactic education, and a Q&A section to evaluate the participants’ understanding of the key concepts. During the CHF didactic education, participating dyads will receive CHF education information provided by the staff nurse. The contents of the CHF education have been mapped based on the latest national clinical practice guideline for CHF (23). Apart from information on CHF self-care, the control group will receive additional knowledge on CHF, involving the definition of CHF, epidemiology, diagnosis, comorbidity, and treatment.

Prior to the sessions, dyads will be provided with one set of CHF self-care materials, including two salt spoons, one portable pill box, a scale and cup measurement, and a hard copy of handouts. The handouts for the control group consist of information on CHF self-care and homework assignments using well-established questionnaires, such as the heart failure knowledge test (67), the Dutch Heart Failure Knowledge Scale (68), and the heart failure specific health literacy scale (69) . Table 1 lists a summary of the ACT group and CE group for CHF patients and their FCs.

**Table 1.** Summary of the ACT group and CE group sessions

| **Session** | **ACT group (Intervention group)** | **CE group (Control group)** |
| --- | --- | --- |
| Week 1  Session 1 | - Introduction to the sessions, guidelines, and group expectations - Introducing and practicing mindfulness when eating raisins - Exploring the control agenda: identifying issues, the normalcy of psychological suffering, unworkability of the control-based strategies by practicing guided mindfulness to revisit a challenging moment during the CHF management process in the family context - Introducing the paradoxical effects of control-based strategies and acceptance as an alternative by using the metaphor of quicksand - Providing an overview of CHF self-management and symptom monitoring - Homework assignment: to identify challenging moments and be aware of inner events | - Introduction to the sessions - Providing information on CHF facts and self-management - Definition of heart failure - Terminology of heart failure - Heart failure epidemiology and prognosis - Key steps in the diagnosis of CHF - Importance of CHF self-management* - Importance and strategies of monitoring symptoms* - Reviewing the main concept taught in this session based on the following questions   What are your symptoms of CHF?  Why is it critical to check the signs and symptoms of CHF every day?  How do you plan to watch for your signs and symptoms of CHF every day?   - Homework assignment: adopted the heart failure knowledge test (67) |
| Week 2  Session 2 | - Practicing mindfulness when listening - Reviewing the previous session - Clarifying personal values with a “value in trash” exercise and exploring how individuals may choose to respond to negative thoughts/feelings about managing CHF in a value-consistent manner - Exploring the unworkability of attempts to avoid or control negative internal experiences (e.g., relationships, thoughts, feelings) and how these efforts lead to value-inconsistent actions and impaired quality of life by illustrating the metaphor of “the passengers on the bus” - Providing information on recognizing the most common cardiac medication regime, the correct use and possible side effects, and the importance of medication adherence and possible solutions - Homework assignment: identify an alternative behavior they are willing to perform that would help them move toward their core values | - Reviewing the previous session - Providing information on CHF pharmacological treatment and medication adherence - Pharmacological treatment for CHF - Correct use and possible side effects* - Importance of medication adherence and possible solutions* - Reviewing the main concept taught in this session based on the following questions   What is the name of your ordered medicine?  Why is it important to take your medicine every day?  How will you remember to take your water pill every day?   - Homework assignment: adopted the Dutch Heart Failure Knowledge Scale (68) |
| Week 3  Session 3 | - Practicing mindfulness when breathing - Reviewing the previous session - Identifying an alternative behavior they are willing to perform that would help them move towards their core values - Exploring possible inner barriers (e.g., cognitive or emotional) to taking these committed actions - Promoting detachment from unhelpful thoughts, feelings, and prior relationship experience about CHF and CHF management in the context of home care by engaging in defusion exercises, including “thoughts on the cards” and a “tug of war” - Providing information on the importance of fluids and dietary management, a low-sodium diet, and tips on selecting food every day - Homework assignment: establish an action plan for an identified alternative behavior, implement the specific behavior, and be mindful of the response of family members. | - Reviewing the previous session - Providing information on CHF treatment, dietary and fluid management - Cardiovascular and non-cardiovascular comorbidities - Oxygen therapy and ventilatory therapy - Mechanical circulatory support - Heart transplantation and renal replacement - Importance of fluids and dietary management* - Low-sodium diet* - Tips on selecting food every day* - Reviewing the main concepts taught in this session based on the following questions:   What foods should you avoid?  Why is it essential to reduce salt intake?  How do you plan to decrease the sodium in your daily diet?   - Homework assignment: adopted the patient knowledge questionnaire on heart failure (69) |
| Week 4  Session 4 | - Practicing mindfulness in a brief body scan exercise - Reviewing the previous session - Clarifying helpful steps to take for patients and their FCs when painful experiences are aroused - Allowing participants to extend self-understanding and self-compassion to their family members by practicing guided mindfulness and revisiting their past experiences of conflict in the context of family - Summarizing the ACT skills taught in the session - Identifying some possible future challenges and knowing how these skills may be useful - Providing information on CHF physical activities, and cigarette and alcohol consumption | - Reviewing the topics discussed in previous sessions - Providing information on CHF physical activities, and cigarette and alcohol consumption - Advantages and disadvantages of regular physical exercise* - Common principles during exercise* - Monitoring pulse rate to adjust the intensity of exercise* - Recognizing and responding to possible cardiac symptoms during the exercises* - The benefit of smoking cessation and common cessation methods * - Abstaining from excessive alcohol intake* - Reviewing the main concepts taught in this session, based on the following questions   How much of a weight gain should you report to your doctor?  Why is it important to weigh yourself daily?  How can you remember to weigh yourself daily? |

Note: ACT: Acceptance and commitment therapy; CHF: Chronic heart failure; HRQOL: Health-related quality of life. * The content is similar to that in the corresponding session in the intervention group.

